## **11. Statistical Analysis**

### **Sample size**

Statistical tests will be analyzed using SPSS version 23.0 software program (IBM, Armonk, NY) and R Software (Dusseldorf, Germany). Bioinformatic analysis will be performed using bioinformatics pipeline (HumanN2).

### *Fecal Analysis*

Fecal samples will be analyzed using next-generation sequencing technology (Illumina NextSeq500). Analysis and interpretation period is planned to perform at four steps;

extraction of DNA from the samples, preparation of the sequence library, data analysis by sequencing, and interpretation of data using bioinformatics methods, respectively. In the first step, DNA will be extracted from fecal samples using the "Repeated bead beating plus column" method developed by Yu and Morrison [46]. In the second step, samples will be prepared using the modified Nextera XT DNA library preparation protocol (Illumina, California, USA) for Illumina NextSeq shotgun sequencing. DNA sequencing data obtained from FastQ files will first be quality checked to eliminate reading errors caused by human contamination using the NCBI Best Match Tagger (BMTagger).

Low-quality sequencing reads will be trimmed. Poor quality and duplicate reads will be removed using a combination of Picard and SAM tools [47,48]. Taxonomic classifications of trimmed reads will be determined using Kraken [49] and Bracken [50] statistical methods. Functional profiling will be assessed using the Human Microbiome Project Unified Metabolic Analysis Network 2 (HUMAnN2; <http://huttenhower.sph.harvard.edu/humann2>) [51]. Taxonomic and functional analysis will be performed using R (Vienna, 2012) (version 3.5.1). Alpha and beta diversity will be calculated using the vegan package (version 2.5-2) in the R program [52]. A dendrogram will be created using the ape package (version 5.1) in the R program and visualized using iTOL [53]. LEfSe, which allows the identification of pathways or taxa that characterize groups, will be used to identify species and pathways that characterize particular groups [54]. The significance threshold will be set as 0.05 and the LDA effect size threshold of 3 will be used for discriminative features. A heatmap map will be created using the R heatmap package to visualize the functional paths in HUMAnN2 [55].

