#### **5. Selection of participants**

Volunteer ultra-marathoners will be recruited from the websites of the organizers of ultra-marathon events, vegan communities, runner magazines, and online running communities. In order for them to be eligible for the study, participants will need to take part in the Sri-Chinmoy ultra-marathon race in Basel, Switzerland. Potentially eligible participants will be identified by research staff. Ten vegan and ten omnivore participants will be randomly selected to enroll in the study using computer-generated random numbers. Randomization

and allocation will be performed by an independent researcher. The study will take place in Zurich and Basel, Switzerland.

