## **8. Primary Outcomes**

1. Intestinal microbial adaptation according to applied diet evaluated by analysing faecal samples taken seven days before and seven days after the race using shotgun metagenomic analysis.

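### Species and pathways are called discriminative at 0.05 per feature plus LDA 3, with no stated multiplicity control, under the only decision rule given for the metagenomic primary outcome

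*Protocol*

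**What the plan says.** Section 8 defines the primary outcome as "Intestinal microbial adaptation according to applied diet evaluated by analysing faecal samples taken seven days before and seven days after the race", by shotgun metagenomics. It names no single taxon, pathway or index.

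Section 11, Fecal Analysis, lists the analyses of these samples. Diversity is only computed: "Alpha and beta diversity will be calculated using the vegan package", with no test or threshold attached. A dendrogram and a heatmap are for display. LEfSe "will be used to identify species and pathways that characterize particular groups", and the next sentence sets its two cut-offs: "The significance threshold will be set as 0.05 and the LDA effect size threshold of 3 will be used for discriminative features". A feature must meet both.

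The protocol mentions no false-discovery or family-wise control and gives no number of features. Section 5 sets the groups: "Ten vegan and ten omnivore participants will be randomly selected to enroll in the study".

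**The concern.** A shotgun profile normally yields many species and many functional pathways. A 0.05 threshold applied to each feature bounds the error for that feature, not for the list. The LDA cut-off does not repair this. It sits on an abundance scale, so it removes mainly rare features and leaves chance differences in abundant ones.

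What is at stake is how the list will be read. Section 13 foresees using the findings either to support vegan diets for athletes or to warn of their harms. A list that would usually contain some diet-characterising species even if diet made no difference can support neither message.

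This is not a detail left to a later document. The protocol itself writes down the rule, with both cut-offs, in its statistical section.

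**Working it through.** The protocol states no power or family-wise error figure, so there is nothing to reproduce.

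**Inputs from the protocol.** Threshold 0.05; LDA threshold 3; 10 vegan and 10 omnivore runners.

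**Assumed inputs.** The number of features m (50 to 400), the abundance distribution, the correlation between taxa, and a rank test (Kruskal-Wallis for two groups) for each feature.

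**Step 1: the 0.05 criterion alone, independent features, no true difference.**
Expected false positives = 0.05 × m. P(at least one) = 1 − 0.95^m.

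| m | Expected false positives | P(at least one) |
|---|---|---|
| 50 | 2.5 | 0.923 |
| 100 | 5 | 0.994 |
| 200 | 10 | >0.999 |
| 400 | 20 | >0.999 |

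The probability passes 95% at m = 59 and 99% at m = 90.

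**Step 2: does n = 20 cause this?** The simulated size of the rank test with 10 against 10 was 0.051, close to nominal. Each test behaves properly, and the inflation comes from m.

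**Step 3: both criteria together.** Null communities were simulated with log-normal abundances, 80% prevalence and 200 runs per setting. The LDA score was approximated by log10(1 + half the difference in group means), with abundances scaled to 1,000,000. Ranges cover the abundance spreads tried.

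| m | P(at least one false feature) | Mean number of false features |
|---|---|---|
| 50 | 0.72–0.90 | 1.3–2.1 |
| 100 | 0.80–0.99 | 1.7–3.5 |
| 200 | 0.92–1.00 | 2.7–4.7 |
| 400 | 0.96–1.00 | 3.2–6.4 |

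The LDA filter therefore removes many false hits (at m = 400, from about 20 to 3–6) but seldom all of them.

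**Step 4: sensitivity.** Further null simulations varied the LDA approximation, the abundance spread and the correlation between taxa. With blocks of 10 taxa and within-block correlation 0 to 0.6, the probability was 0.83–0.94 at m = 100 and 0.96–1.00 at m = 400. The widest set used five large clusters with correlation 0 or 0.5. It gave 0.70–0.98 at m = 100, 0.79–1.00 at m = 200 and 0.85–1.00 at m = 400. Taken together, the range is about 0.7–0.99 at 100 features and 0.85–1.00 at 400.

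**Step 5: with adjustment.** With Benjamini-Hochberg at 5%, the Step 3 simulations gave at least one false feature in 0 to 0.04 of runs.

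**Step 6: what adjustment costs.** A lone true feature must reach p ≤ 0.05/m. There are 184,756 ways to split 20 runners 10 and 10. For m = 200 the limit is 0.00025. The exact two-sided rank-sum p-value is 2 × 19/184,756 = 0.00021 at U = 5 and 2 × 30/184,756 = 0.00032 at U = 6. So U must be 5 or less on a 0-to-100 scale, which is near-complete separation of the diets.

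The chi-square approximation is stricter. Complete separation gives rank sums 55 and 155, H = (12/420) × (55²/10 + 155²/10) − 63 = 14.29, and p = 0.00016. Since 0.05/0.000157 ≈ 318, a lone feature could never pass with more than 318 features.

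**The case against.** **Silence on adjustment.** A reader might infer that the protocol prescribes raw p-values. It does not say so. The text is silent on whether 0.05 applies to raw or adjusted values, and a statistical analysis plan that is not shown might add false-discovery control. This limits the point to no stated control. It does not remove it, because the rule as written can be followed literally.

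**Exploratory purpose.** LEfSe is described as characterising groups, which is feature discovery, and it is never named as the primary test. It is also tempting to say that the primary outcome will come out positive whatever the truth. The documents do not support that, since no passage sets a success criterion. What stands is that this is the only decision rule attached to the primary outcome, and that the list is not labelled exploratory.

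**Certainty.** A reader might call false discoveries almost certain. That needs a feature count the protocol does not give, and it leaves out the LDA criterion in the same sentence. With both criteria and correlated taxa, the chance at 100 features can be as low as about 0.7.

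**Sample size.** It is tempting to blame the 20 runners. Step 2 shows that the size of each test is right. Small groups cost power and precision instead.

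**Contrast.** Section 8 concerns change from before to after the race, and the groups LEfSe will compare are not defined as diet alone. The simulation is a single two-group comparison. Further contrasts would add families of tests, but the figures do not describe them.

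**Conclusion.** The point holds in this form: the protocol fixes a per-feature threshold of 0.05 plus LDA 3 for species and pathways, states no multiplicity control, and offers no other decision rule for its metagenomic primary outcome. If no diet difference exists, at least one falsely discriminative species is likely to very likely over 100 to 400 species. Pathways come on top of that.

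The figures rest on an assumed feature count, log-normal abundances, an approximate LDA score and a single vegan-versus-omnivore comparison. The direction does not depend on these choices, because an effect-size cut-off does not control an error rate.

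**What to change.** Amend the threshold sentence in Fecal Analysis before results are seen:

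- Apply a prevalence/abundance filter whose limits are fixed in advance.
- Apply the 0.05 threshold to Benjamini-Hochberg adjusted p-values, separately for species and for pathways.
- Keep LDA 3 as an additional effect-size criterion.
- Report features that meet only the raw 0.05 plus LDA 3 rule as exploratory, not as evidence of a diet effect.

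This takes a short change of text and one further calculation, with no new samples. The real cost is yield: with 10 per group, few features will pass. Exact or permutation p-values would avoid the floor of the chi-square approximation shown in Step 6.

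If that loss is unacceptable, a defensible alternative is to name one primary microbiome measure with its own test and label the whole LEfSe search exploratory.

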### **13. Originality of the research**

Although the vegan diet has been widely preferable and studies claiming to be adequate for ultra-endurance athletes, there is still no comprehensive investigation of the impact of the vegan diet applied by ultra-endurance athletes. Therefore, we aim to provide an in-depth investigation of vegan diets by analyzing blood and fecal analysis in ultra-endurance athletes adhered to this diet for the long term. In case of vegan diets are found to be beneficial and sufficient, the study a level of evidence against the belief that the vegan diet may be insufficient for athletes and may provide the framework for future studies to assess veganism's effects in athletic populations. Besides, the athletic population consumes meat products 2- and more fold according to the other individuals. If a Vegan diet provides enough energy availability and balance macro- and micronutrients in the body, we can also recommend consuming the diet for the future of planet-saving. On the other hand, if vegan diets are detrimental for either metabolism, including immunologic or oxidative factors or gut-host crosstalk, veganism's adverse effects could be identified to inform athletes to inhibit its detrimental consequences.

By adding the measurements of oxidant/antioxidant- and muscle fatigue-related parameters, we seek to explore the impact of dietary patterns on body hormesis and fatigue levels in ultra-endurance athletes. Dietary intake data will analyze all diet composition, including nutrient and non-nutrient components, the main determinants of antioxidant defense. We may also determine whether the whole dietary pattern or food intake affects hormesis balance and endogenous antioxidant defense in athletes endured under extreme conditions.

